| Criteria for deferral of administration | 
In cases where any of the following criteria are met, the PI or SI may postpone the administration of the auto-DC/Gal or the iPS-NKT cells for up to 3 days.
 
 
1) The PI or SI determines that administration of the DC/Gal or iPS-NKT cells is inappropriate.
 
2) All adverse events occurring after the administration of the auto-DC/Gal or the iPS-NKT cells do not recover to a manageable Grade 2 or Grade 1 or below, or to baseline.
 
3) Infectious disease requiring treatment develops within 24 hours prior to the administration of iPS-NKT cells, including the development of fever of 38°C or higher.
 
                                                                                                                                                                                                                                                                                                                                                                                                                                                                                                                                                                                                                                                                                                                                                                                                                                                                                                                                                                |

|                                                  |                                                                                                                                                                                                                                                                                                                                                                                                                                                                                                                                                                                                                                                                                                                                                                                                                                                                                                                                                                                                                                                                                                                                                                                                                                                                                                                                                                                |
|--------------------------------------------------|--------------------------------------------------------------------------------------------------------------------------------------------------------------------------------------------------------------------------------------------------------------------------------------------------------------------------------------------------------------------------------------------------------------------------------------------------------------------------------------------------------------------------------------------------------------------------------------------------------------------------------------------------------------------------------------------------------------------------------------------------------------------------------------------------------------------------------------------------------------------------------------------------------------------------------------------------------------------------------------------------------------------------------------------------------------------------------------------------------------------------------------------------------------------------------------------------------------------------------------------------------------------------------------------------------------------------------------------------------------------------------|
| Criteria for drug suspension                     | 
If any of the following criteria are met, the PI or SI will discontinue administration of DC/Gal or iPS-NKT cells. If administration is discontinued, the patient will be shifted to the observation period from the date when the decision to discontinue administration was made, and testing and evaluation will be continued in accordance with the testing schedule.
 
 
1) DLT occurs after the auto-DC/Gal administration, or all adverse events of Grade 3 or higher that occurred during the study period do not recover or improve to Grade 1 or clinically manageable Grade 2 by the time immediately prior to the auto-DC/Gal or the iPS-NKT cell administration.
 
2) Infectious disease requiring treatment develops and does not recover or improve to Grade 1 or clinically manageable Grade 2 by the time immediately prior to administration of DC/Gal or iPS-NKT cells.
 
3) SpO2 (room air) is maintained below 90 %
 
4) Grade 2 or higher on the mMRC shortness of breath scale in the examination before the auto-DC/Gal or the iPS-NKT cell administration
 
5) Discontinuation request from the subject
 
6) Otherwise in which the need for discontinuation of the auto-DC/Gal or the iPS-NKT cell administration to the subject by the PI or SI.
 
 |
| Criteria for study discontinuation of subject    | 
 
1) When progression of the primary disease requiring concomitant use of prohibited drugs or therapy is recognized, as judged by the PI or SI.
 
2) Discontinuation requests from the subject
 
3) When the subject is found to be ineligible after enrollment.
 
4) Otherwise in which the PI or SI determines that the subject is unable to receive the auto-DC/Gal
 
                                                                                                                                                                                                                                                                                                                                                                                                                                                                                                                                                                                                                                                                                                                                                                                                                                                                                                                                    |
| Prohibited concomitant drug and therapy          | 
 
• Corticosteroids, immunosuppressive drugs, other antineoplastic drugs, radiation therapy, or surgery including tumor resection.
 
• Any transfusion therapy (however, if the above drugs or therapies are necessary in response to an adverse event thought to be caused by DC/Gal or iPS-NKT cells, the above drugs or therapies may be used with the adverse event as DLT)
 
                                                                                                                                                                                                                                                                                                                                                                                                                                                                                                                                                                                                                                                                                                                                                                                                                                                                                                                                         |
| Duration of study participation for each subject | The study period for each subject will be from the date consent is obtained to the end of the last observation. If the subject requests to discontinue the study or if it becomes difficult to observe or conduct the study due to transfer to a different hospital or other reasons, the date of discontinuation and the date of completion of the final observation shall be the date of discontinuation and the date of completion of the final observation.                                                                                                                                                                                                                                                                                                                                                                                                                                                                                                                                                                                                                                                                                                                                                                                                                                                                                                                |
| Sample size                                      | 2~12                                                                                                                                                                                                                                                                                                                                                                                                                                                                                                                                                                                                                                                                                                                                                                                                                                                                                                                                                                                                                                                                                                                                                                                                                                                                                                                                                                           |
| Study duration                                   | After completion of the study notification to MHLW – 03/31/2027                                                                                                                                                                                                                                                                                                                                                                                                                                                                                                                                                                                                                                                                                                                                                                                                                                                                                                                                                                                                                                                                                                                                                                                                                                                                                                                |

|                                    |                                                                                                                                                                                                                                                                                                                                                                                                                                                                                                                                                                                                                                                                                                                                                                                                                                                                                                                                                                                                                                                                                                    |
|------------------------------------|----------------------------------------------------------------------------------------------------------------------------------------------------------------------------------------------------------------------------------------------------------------------------------------------------------------------------------------------------------------------------------------------------------------------------------------------------------------------------------------------------------------------------------------------------------------------------------------------------------------------------------------------------------------------------------------------------------------------------------------------------------------------------------------------------------------------------------------------------------------------------------------------------------------------------------------------------------------------------------------------------------------------------------------------------------------------------------------------------|
| Number of study site               | Single site: Chiba University Hospital                                                                                                                                                                                                                                                                                                                                                                                                                                                                                                                                                                                                                                                                                                                                                                                                                                                                                                                                                                                                                                                             |

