### 1.2.7. Expected Side Effects

The main "side effects" expected in relation to DC/Gal or iPS-NKT cells and examples of treatments are listed below.

- ① Elevated blood pressure: Antihypertensive agents should be administered according to symptoms and severity.
- ② Fever: Blood test, chest X-ray, blood culture should be performed. Regarding the possibility of infectious disease, antibiotic agents should immediately be administered. Antipyretics should not be administered if there is no febrile distress but should be given as needed if febrile distress is marked.
- ③ Respiratory distress: Administer oxygen promptly to stabilize blood oxygenation. Blood tests, X-rays and CT scan (contrast if possible) should be performed as part of the screening for the diagnosis. Possible causes of severe respiratory failure during infusion include allergic and embolic events (especially when iPS-NKT is administered). Steroids and epinephrine should be administered according to the severity of the disease, as well as antithrombotic therapy for embolism.
- ④ Shock: The physician in charge and the attending physician will respond promptly. Check vital signs, perform blood tests, and administer steroids or epinephrine according to the severity of the illness. Administer oxygen and pressor agents for respiratory failure and hypotension, depending on the severity of the illness.
- ⑤ Pharyngeal fistula: Since pharyngeal fistula associated with tumor shrinkage was observed in a previous study of combination therapy with autologous NKT cells and DC/Gal, this adverse event should be kept in mind in this study as well. If this adverse event is observed, infection prophylaxis and, if necessary, pharyngeal fistula closure should be performed.
- ⑥ Cerebral infarction: Because the cells are administered into the arteries of the neck, there is a possibility of blood clots flowing into the brain during cannulation. The patient should be evaluated after consulting a neurosurgeon for functional impairment, checking vital signs, and administering cerebro-protective drugs.
- ⑦ Bleeding and hematoma at the puncture site: This may occur with arterial puncture of the cannula. If severe hematochezia develops, consult a plastic surgeon and consider removal of hematochezia. Mild to moderate hematomas can be absorbed with observation.

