## 5.2. Dose Limiting Toxicity (DLT)

DLT is defined as the following adverse events observed during the DLT assessment period, in which a causal relationship with auto-DC/Gal or iPS-NKT cell cannot be denied. Grading is determined according to the CTCAE ver.5.0 translated in Japanese by the Japan Clinical Oncology Group (JCOG).

- 1) Grade 4 or higher hematological toxicities
- 2) any non-disease-related blood toxicity requiring any transfusion or granulocyte-colony stimulating factor (G-CSF) administration
- 3) grade 3 or higher non-hematological toxicities (excluding transient clinical laboratory abnormalities, diarrhea, nausea, vomiting, or other manageable systemic symptoms that recovered to grade 2 or below under appropriate treatments)
- 4) AEs lead to blood transfusion.

If the PI suspects the occurrence of DLTs, the PI can consult the Independent Data Monitoring Committee (IDMC), and the IDMC determines the continuation or termination for the patient. Subjects who do not complete the DLT assessment period for reasons other than DLT will not be considered DLT evaluable cases and then another

subject will be supplemented in the same dose cohort.

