## 5.10. Concomitant drugs and therapy

### 5.10.1. Permitted concomitant drug/therapy

- Palliative and supportive care for the primary disease
- Palliative radiation therapy for local pain management may be administered during the study if:
  - The irradiated area covers less than 10% of the total bone marrow
  - The irradiation field does not include the evaluation lesion
- Any transfusion therapy as a response to adverse events thought to be caused by DC/Gal or iPS-NKT cell. Such adverse events shall be considered DLT.

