### 5.10.3. Prohibited drug/therapy

In this study, DC/Gal or iPS-NKT cell will not be administered in combination with the following drugs or therapies. If it is necessary to use them clinically, it should be treated as a deviation to avoid immediate risk and reported to the record and the head of the medical institution.

- Corticosteroids (methylprednisolone 10 mg/day or more or equivalent) or immunosuppressive drugs taken or injected, other antineoplastic agents, radiation therapy, or surgery including tumor resection

- Any transfusion therapy (except as noted in 5.10.1).

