### 10.1.3. Subject population conforming to the research protocol (per protocol set : PPS)

Subjects without the following serious violations of the provisions of the research protocol, including study methods and concomitant therapies.

Violation of selection criteria, exclusion criteria, concomitant use of prohibited drugs, or concomitant use of prohibited therapies

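### One parenthesis in the synopsis row on prohibited therapy defines a wider set of DLTs than the synopsis DLT row and sections 5.2 and 5.10, so the event set behind the primary endpoint is not unique

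*Protocol*

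**What the plan says.** **Synopsis, prohibited concomitant drug and therapy.** The first bullet lists "Corticosteroids, immunosuppressive drugs, other antineoplastic drugs, radiation therapy, or surgery including tumor resection", with no steroid dose threshold. The second bullet adds transfusion and carries a parenthesis: "if the above drugs or therapies are necessary in response to an adverse event thought to be caused by DC/Gal or iPS-NKT cells", then "the above drugs or therapies may be used with the adverse event as DLT". It states no grade.

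**Synopsis DLT row and section 5.2.** Both give the same four items: hematological toxicity of grade 4 or higher; non-disease-related blood toxicity requiring transfusion or G-CSF; non-hematological toxicity of grade 3 or higher; and events leading to transfusion. The third item has an exclusion that includes "other manageable systemic symptoms that recovered to grade 2 or below under appropriate treatments".

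**Section 5.10.1.** Transfusion in response to a product-related event is permitted, and "Such adverse events shall be considered DLT". No other treatment is given this status.

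**Section 5.10.3.** Corticosteroids are prohibited from 10 mg/day methylprednisolone equivalent, together with immunosuppressants, antineoplastics, radiation and surgery. If one is clinically necessary, "it should be treated as a deviation to avoid immediate risk". The only exception refers back to transfusion in 5.10.1.

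**Section 1.2.7.** Steroid treatment of an expected side effect is foreseen. For respiratory distress, "Steroids and epinephrine should be administered according to the severity of the disease", and shock is handled similarly.

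**The concern.** Section 10.5.2.1 computes the primary analysis from the definition of DLT, and the same count drives the 3+3 rule. The protocol should therefore yield one answer to whether a given event is a DLT. For a product-related event managed with a steroid or another listed treatment, it can yield two.

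DLT status also acts on the individual subject. Under 5.9.1, a DLT after auto-DC/Gal stops further administration. Under 5.2, a subject who leaves the assessment period early for a reason other than DLT is not evaluable and is replaced. The classification can therefore affect what a subject receives and who is in the denominator, as well as the numerator.

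**Working it through.** **Step 1. The passages side by side**, for a product-related event in the DLT assessment period.

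| Place | Treatments that make the event a DLT | Status of necessary steroid use |
|---|---|---|
| Synopsis, prohibited therapy row (literal reading) | Steroids at any dose, immunosuppressants, antineoplastics, radiation, surgery, transfusion | Permitted, event is a DLT |
| Synopsis DLT row and 5.2 | Transfusion, G-CSF | Not a criterion |
| 5.10.1 | Transfusion | Not mentioned |
| 5.10.3 | None stated | Deviation, from 10 mg/day methylprednisolone equivalent |

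**Step 2. Where the two event sets differ.** Take a product-related event that needs a listed treatment other than transfusion. It is a DLT under the literal parenthesis but not under 5.2 if it is:
- non-hematological, grade 1 or 2;
- non-hematological, grade 3 or higher, but within the exclusion in item 3;
- hematological, below grade 4, without transfusion or G-CSF.

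A non-hematological event of grade 3 or higher outside the exclusion, or a hematological event of grade 4 or higher, is a DLT under both.

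**Step 3. The decision margin.** The planned 2 to 12 subjects reproduce: the maximum is 2 doses × 6 = 12, and the minimum is 2 because two DLTs already meet the stop rule. Within a dose, the limit lies between one and two DLTs. With exact (Clopper-Pearson) 95% intervals:
- 1/6 = 16.7% (0.4% to 64.1%): tolerable;
- 2/6 = 33.3% (4.3% to 77.7%): stop.

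One subject in a category from Step 2 is enough to cross that line.

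**Step 4. Illustration of size.** The protocol gives no DLT rates, so all rates here are assumptions. Let p be the chance that a subject has a DLT. A dose passes with 0/3, or with 1/3 followed by 0/3:

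P(pass) = (1−p)³ + 3p(1−p)² × (1−p)³

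- p = 0.10: 0.729 + 0.177 = 0.906
- p = 0.15: 0.614 + 0.200 = 0.814
- p = 0.20: 0.512 + 0.197 = 0.709
- p = 0.25: 0.422 + 0.178 = 0.600

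Let s be the extra share of subjects who have an event from Step 2 and no DLT under 5.2, so that the rate under the literal parenthesis is p + s.

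| Rate under 5.2 | s = 0 | s = 0.05 | s = 0.10 | s = 0.15 |
|---|---|---|---|---|
| 0.05 | 0.973 | 0.906 | 0.814 | 0.709 |
| 0.10 | 0.906 | 0.814 | 0.709 | 0.600 |
| 0.20 | 0.709 | 0.600 | 0.494 | 0.396 |

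If all six subjects are always treated, the 0.10 row at s = 0 and s = 0.10 becomes 0.886 and 0.655. The pattern is the same.

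**The case against.** **The parenthesis was meant for transfusion only.** This is the strongest objection. It sits in the transfusion bullet, its counterpart in 5.10.1 is confined to transfusion, and 5.10.3 repeats that limit. The intention may well have been the same. But the words refer to drugs as well as therapies listed above, and the drugs stand in the preceding bullet. If only transfusion was intended, the sentence is misworded and still needs correcting.

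**The IDMC decides.** Section 10.6 gives the committee the final judgment on whether an event is a DLT, and 7.1.3.2 has the PI refer suspected cases at once. This makes arbitrary counting less likely. It does not say which of two definitions the committee should apply.

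**The example in 1.2.7 is weak.** This stands in part. That section links steroids to severity, and severe respiratory failure or shock may already be a DLT under 5.2. It shows that steroid treatment is contemplated, not that events in the gap are expected or frequent.

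**The rates are invented.** They are assumptions, so the table includes a small extra share and varies the base rate. The narrow margin between 1/6 and 2/6 is common to any 3+3 rule; what is particular here is that the wording leaves open which subjects count.

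**Conclusion.** The inconsistency is real and touches the primary endpoint and the stopping rule. It is one parenthesis against the synopsis DLT row and sections 5.2, 5.10.1 and 5.10.3. The textual conflict does not depend on any assumed rate. Its effect on the pass probability does: 0.91 falling to 0.81, 0.71 or 0.60 holds only for a 10% rate under 5.2 and an extra 5%, 10% or 15%, with subjects independent and at equal risk.

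A reader might infer more than the protocol supports:
- *That the synopsis as a whole contradicts the body.* It does not: its own DLT row agrees with 5.2.
- *That a steroid-treated event is never a DLT under 5.2.* Need for steroids is not a criterion there, but many severe events qualify by grade.
- *That 5.10.3 gives a third, rival classification.* Deviation and DLT are not mutually exclusive. The conflict with 5.10.3 is between permitted use and deviation, and over the dose threshold.
- *That the per-protocol exclusion distorts the primary result.* Section 10.1.3 lists "concomitant use of prohibited drugs, or concomitant use of prohibited therapies" as a violation, but 10.5 uses that set for efficacy only. DLT incidence is analysed in the DLT evaluation population.
- *That a treated subject has already been misclassified.* Nothing in the protocol shows this.

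**What to change.** Reconcile the two synopsis rows and sections 5.2, 5.10.1 and 5.10.3 to one DLT event set before the next escalation or stopping decision. State in 5.2 whether a product-related event that needs a prohibited drug or therapy counts as a DLT and, if so, whether a corticosteroid threshold applies. Repeat that wording in the synopsis and 5.10. Say in the same place whether such use is permitted or is a deviation.

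Ask the IDMC to check whether any subject already treated had a product-related event managed with a prohibited drug or therapy and, if so, to classify it under the single definition. A general re-adjudication is not needed. Which version is clinically right is for the sponsor and the IDMC.

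The cost is a wording amendment and one limited IDMC check. No subjects or procedures are added, and the 2 to 12 sample size is unchanged.
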